## Abstract

**Background:**

Children with cleft palate often experience impaired speech due to atypical velopharyngeal anatomy following palate repair surgery. While surgical repair aims to restore the function of the palate, more than one-third of cases result in continued velopharyngeal insufficiency (VPI) and require reoperation, which can result in negative psychosocial impacts and financial burden. Common surgical approaches for primary palatoplasty, including intravelar veloplasty and double-opposing Z-plasty, have similar reported rates of VPI. Furthermore, procedure selection occurs without any presurgical imaging and varies by operating surgeon. Surgical decisions are often based on intraoperative judgment rather than objective measures. Structural and functional variables have been associated with speech outcomes in this population, but these data exist independently of one another until the school-age years, failing to establish a direct connection between anatomy and functionality of the velopharynx in toddlers. The current clinical paradigm misses a critical window of opportunity for earlier diagnosis of VPI.

**Objective:**

The purpose of this study is to (1) establish which presurgical anatomical variables are predictive of surgical procedure selection based on perceptual assessment of intraoperative tension for palate repair and (2) determine which postsurgical anatomical features are associated with the greatest diversity in oral stop consonant production at 18 months in children with a repaired cleft palate.

**Methods:**

A total of 30 infants with cleft palate will be recruited prior to palate repair. Within 2 weeks of repair, participants will undergo nonsedated magnetic resonance imaging (MRI) of the velopharynx and produce a home-based speech recording. Participants will complete the same protocol after palate repair at 18 months of age. Data will be analyzed by independent raters following completion of a training protocol. Anatomical dimensions of the velopharynx will be extracted from the MRI scans. The number and diversity of oral stop consonants will be extracted from the speech recordings. Interrater and intrarater reliability will be assessed. Logistic regression will be used to evaluate which presurgical anatomical measurements are predictive of surgical procedure selection. Analysis of covariance will be used to examine whether postsurgical anatomical measurements are associated with diversity of oral stop consonant production.

**Results:**

This project was funded in August 2024. Data collection began in April 2025. As of April 4, 2026, a total of 8 participants had been enrolled, and data analysis had not begun. Results are anticipated in 2027.

**Conclusions:**

This study will use nonsedated MRI to investigate how velopharyngeal anatomy influences surgical decision-making and early speech outcomes. Such knowledge may be useful for presurgical planning and early monitoring of postsurgical speech outcomes in children with cleft palate.

**International Registered Report Identifier (IRRID):**

DERR1-10.2196/97206

## Introduction

### Background

Cleft palate is a common congenital anomaly in the United States, affecting roughly 6 per 10,000 live births. Cleft palate alone occurs in approximately 6 per 10,000 live births, whereas cleft lip with or without cleft palate occurs in approximately 10 per 10,000 live births [1]. A cleft palate can impact multiple aspects of a person’s life, including feeding, hearing, communication, dentition, and psychosocial health. Regarding speech, a combination of surgical and behavioral management is often undertaken to mitigate the long-term impact of cleft palate on a person’s ability to communicate.

Primary palate repair is typically performed at the ages of between 9 and 14 months in the United States [2]. Although age-based surgical protocols are common, practice varies due to individual differences in both the operating surgeon and patient-specific characteristics. Optimal timing remains debated, with earlier repair potentially supporting speech and velopharyngeal outcomes whereas later repair may reduce surgical complexity, facial growth restriction, and anesthesia-related risks [2-4]. Recent literature has increasingly supported earlier repair due to these potential speech benefits, although concerns regarding facial growth restriction and perioperative risks persist [5].

Anatomical restoration is the very premise for current surgical approaches to cleft palate repair. One goal is to create a tension-free closure of the cleft to improve healing and reduce the risk of reopening (ie, palatal fistula [6]). For clefts involving the soft palate, surgery should include reconstruction of the levator veli palatini (LVP) muscle. The LVP muscle, which functions to elevate and retract the soft palate, assists in the closure of the velopharyngeal port. Both intravelar veloplasty (IVV) and Furlow double-opposing Z-plasty (DOZ) are widely used techniques to reconstruct the LVP muscle [6]. IVV focuses on levator sling reconstruction with retropositioning and transverse reorientation of the muscles, whereas DOZ combines levator muscle repositioning with soft palate lengthening through opposing Z-plasty flaps. A systematic review by Timbang et al [7] found that outcomes following cleft palate repair vary by cleft type, with DOZ associated with lower rates of secondary velopharyngeal surgery compared with IVV. One way of reducing tension is to base the surgical plan on patient anatomy, where the surgeon determines procedure type based on the perceived tension of the palatal tissue in the operating room; as DOZ requires overlap of the LVP muscle bundles, it can produce a greater amount of tension on the incision site [7]. Beyond the surgeons’ informal assessment of tension intraoperatively, we do not know whether the child’s presurgical anatomy plays a role in their postrepair outcome, and there is no data-driven approach to choosing one surgical technique over another.

Some children still require additional surgical intervention due to remaining velopharyngeal insufficiency (VPI) after primary palatoplasty. VPI is an anatomical deficiency where the velopharyngeal port cannot adequately close to fully separate the oral and nasal cavities during speech and/or swallowing. VPI results in hypernasality, nasal air emission, and/or weak pressure consonants. Children with VPI are also at greater risk of compensatory articulation errors, which are abnormal, learned sound substitutions [8]. All these speech issues impact a person’s ability to communicate effectively. Rates of VPI range widely among hospitals, regions, and countries between 13% and 40% [9,10]. Inability of the initial palate repair surgery to address VPI places children at risk of long-term psychosocial challenges and increases the likelihood of additional costly interventions [11-13]. Even children with otherwise successful repairs often require speech therapy, with 34% to 68% exhibiting cleft speech characteristics [14-16].

Despite advances in surgical training and multidisciplinary cleft care, the incidence of speech disorders after repair has remained high for decades [17]. The timing and technique of primary palatoplasty have been shown to influence surgical outcomes [18]; however, these do not fully explain why some children continue to experience speech difficulties. Earlier repairs tend to result in reduced hypernasality and improved consonant production [14,19], but not all studies agree, with some reporting no clear age effect in secondary VPI surgery [3]. Recent prospective evidence further supports an association between timing and early speech sound development, particularly oral stop consonant production. A recent study of 113 infants with repaired cleft palate revealed that at least one oral stop was evident in the consonant inventory for 84% of children at 16 months, 71% produced 2 or more different stops, and only 7% produced all 6 stop consonants [20]. This represents a gap in the literature supporting early surgical and speech outcomes for children with cleft palate.

Cleft palate repair aims to restore functional separation of the oral and nasal cavities to support speech development through reconstruction of the soft palate. Common approaches include IVV to reposition the levator musculature and DOZ, which uses opposing Z-shaped flaps to both lengthen the soft palate and improve muscular alignment; both are typically performed in conjunction with primary palatoplasty techniques such as the 2-flap or similar layered closure approaches. Both techniques are widely used in clinical practice, but comparative studies have not established a consistently superior approach, with outcomes varying across patient populations and study designs [7,21].

### Innovation in Magnetic Resonance Imaging–Based Assessment

The clinical gold standard for assessing VPI is perceptual evaluation and nasopharyngoscopy, which is commonly not possible in children under 3 years of age due to reduced speech complexity and compliance [22,23]. Magnetic resonance imaging (MRI) offers a noninvasive method to visualize palatal musculature in vivo and has been successfully applied to study cleft palate in both adult [24-28] and pediatric populations [29-31]. Nonsedated MRI protocols, when combined with behavioral preparation, improve compliance and procedural success in infants, enabling assessments both before and after palate repair. This provides the opportunity to connect patient-specific anatomical features with early speech outcomes. MRI-based assessment in infants has the potential to help identify VPI risk much earlier than the current clinical timeline allows. Additionally, using MRI to quantify surgical outcomes moves beyond subjective perceptual assessments, which are prone to bias, and supports data-driven, individualized surgical planning and monitoring. Nonsedated MRI also addresses the limitations of conventional imaging methods such as sedation-related cognitive risks, radiation exposure, and invasiveness.

MRI of the velopharynx is becoming increasingly accepted to assess older children with VPI [32,33], but it has not yet been applied clinically to children under 4 years of age. Most prior research has focused on VPI rates or surgical technique comparisons rather than exploring the mechanisms behind these speech deficits [17]. Understanding velopharyngeal development in typical populations reveals substantial variability in timing and sound-specific closure patterns [34], highlighting the need for studies focusing on these underlying mechanisms. This study aims to fill these gaps by using MRI to connect individual anatomy to early speech development in children with cleft palate.

### Aims of This Study

In summary, recent studies quantifying the velopharynx in children have generally examined anatomy and physiology in isolation [35], and many have relied on cross-sectional designs [15,32]. Few have tracked both anatomical and functional measures at 2 time points within the same individual. Multidimensional data before and after palatoplasty are crucial for understanding how palate repair influences both velopharyngeal structure and function. These individualized assessments are key for translating basic science findings into patient-specific surgical planning and targeted interventions. This protocol aims to take an essential step toward precision medicine in infants with cleft palate.

This study combines nonsedated MRI–based anatomical assessment with functional speech measurements in the same infants before and after palatoplasty. By linking patient-specific anatomy before and after palate repair to early speech outcomes, we aim to establish data-driven criteria for individualized surgical planning and targeted speech monitoring. This approach addresses a critical gap by providing quantitative, objective measures of surgical success and velopharyngeal development, moving beyond subjective assessment. Ultimately, these findings may lead to work that reduces persistent speech deficits, prevents multiple surgeries, and lessens the associated psychosocial and financial burden of cleft palate. Specifically, this study has two primary aims:

To establish which presurgical anatomical variables are predictive of surgical procedure selection based on perceptual assessment of intraoperative tension for palate repair (hypothesis: preoperative cleft width and LVP muscle length are predictive of surgical procedure selection based on intraoperative tension of palatal tissue)To determine which postsurgical anatomical features are associated with the greatest diversity in oral stop consonant production at 18 months in children with repaired cleft palate (hypothesis: a longer velum, greater effective velopharyngeal ratio, and continuity of the LVP muscle are associated with greater diversity of oral stop consonants by 18 months but not with procedure type)

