### Participants and Recruitment

A total of 30 participants will be recruited from the Children’s Hospital Colorado Cleft Lip and Palate Program (Aurora, Colorado), with an initial enrollment of 39 to account for an anticipated 30% attrition due to MRI motion artifacts, refusal, or missed visits. This sample size was selected based on the pilot nature of this work and use of a single recruitment site; furthermore, the sample size is consistent with prior prospective studies using nonsedated MRI of the velopharynx in children [33,36,37]. This study is considered exploratory to evaluate the relationship among anatomy, surgical selection, and early speech outcomes, as well as to support future larger-scale, multicenter studies. The recruitment site receives 50 to ⁠60 new referrals each year, providing ample opportunities to reach the target sample size over the 3-year funding period. Retention strategies will be used to reduce dropout, including regular personalized reminders, flexible scheduling, and incentives. Participants must be from English-speaking families and have a diagnosis of cleft palate that has not yet been repaired. Infants diagnosed with syndromes prior to 18 months (as reported in their medical chart), those ineligible for MRI (eg, metal implants or severe airway anomalies), or those with other contraindications to standard surgical care will be excluded. Those scheduled for primary palatoplasty after 15 months of age will also be excluded from this analysis.

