### Surgical Considerations

Participants will undergo primary palatoplasty within a typical early palate repair window prior to 15 months [38]. Two standard surgical approaches will be evaluated: IVV and Furlow DOZ. These 2 procedures are commonly used for primary palatoplasty at the study site. Due to the observational nature of this study, no standardization or changes to the surgeons’ procedures will take place; however, individual variability will be accounted for by recording the operating surgeon of each participant and controlling for any significant differences between surgeons in the analysis. Both procedures aim to restore the LVP “sling” to its intended anatomical position in the posterior velum but differ in technique. IVV reorients the muscle bundles end to end without overlap and closes the mucosa with a straight-line suture. DOZ repositions the LVP muscle via opposing Z-shaped incisions, lengthening the velum and creating overlap of the muscle bundles. All surgeries will be performed at a single institution by 1 of 5 operating surgeons. Procedure selection and the use of tissue adjuncts will be determined intraoperatively based on the surgeon’s clinical expertise, which may include a perceptual assessment of the amount of palatal tissue and/or tension upon closure of the cleft defect; no randomization will be performed. Tissue adjuncts, in this context, refer to flaps or grafts added to the palate from an alternate location in the mouth (eg, buccal fat pad flap or buccal myomucosal flap).

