**Figure 2 figure2:**
[figure not shown]
Presurgical magnetic resonance image of an infant labeled with cleft palate with cleft width (A) and levator veli palatini (LVP) muscle length (B).

Through aim 2, we will compare velopharyngeal function for speech among infants with repaired cleft palate following different repair techniques using both perceptual (oral stop production) and objective (anatomical) measures of the velopharynx [29,31]. Given that surgery is an anatomical solution to a physiological concern (aberrant speech), it is essential to establish a link between anatomy and physiology in infants and toddlers to facilitate early diagnosis and remediation of VPI in this population. We further hypothesize that anatomical parameters such as a longer velum, greater effective velopharyngeal ratio, and continuity of the LVP muscle (Figure 3) may be associated with greater diversity of oral stop consonants by 18 months. If this hypothesis is accurate, postoperative anatomy of children with repaired cleft palate could be used as a complement for speech production when it comes to considering secondary surgical intervention. Identifying the relationship between postoperative anatomy and velopharyngeal function in toddlers offers a critical opportunity to intervene earlier and improve speech outcomes in this population. These multidimensional data may provide additional confidence in referring for secondary surgical intervention at an earlier age, when speech production is more limited in clinical visits.

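### The Aim 2 hypothesis includes a no-association clause about procedure type that is ambiguous and that about 27 to 30 non-randomised infants cannot support

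*Protocol article*

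**What the plan says.** In Aims of This Study, the Aim 2 hypothesis names velar length, effective velopharyngeal ratio and levator continuity and says they "are associated with greater diversity of oral stop consonants by 18 months but not with procedure type". No equivalence margin accompanies the clause.

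Other statements that bear on it:

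- Surgical Considerations describes DOZ as "lengthening the velum and creating overlap of the muscle bundles". Of allocation it says that "no randomization will be performed": the surgeon decides during the operation, and the decision may rest on the amount of palatal tissue and on tension at closure.
- Background cites a systematic review that found "DOZ associated with lower rates of secondary velopharyngeal surgery compared with IVV". Background also says that comparative studies have shown neither technique to be consistently better, and the Abstract says reported velopharyngeal insufficiency rates are similar.
- Statistical Analysis plans a 2-way analysis of covariance for Aim 2. Postsurgical anatomical measures are the outcome, surgical type and number of oral stops are the factors, and sex, cleft type and developmental and language scores are controlled for.
- Participants and Recruitment sets the size: "A total of 30 participants will be recruited from the Children’s Hospital Colorado Cleft Lip and Palate Program", "with an initial enrollment of 39 to account for an anticipated 30% attrition due to MRI motion artifacts, refusal, or missed visits". The basis given is "This sample size was selected based on the pilot nature of this work and use of a single recruitment site".
- Discussion, Expected Findings, says of Aim 2 that "we will compare velopharyngeal function for speech among infants with repaired cleft palate following different repair techniques". It then restates the hypothesis without the words on procedure type.

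**The concern.** A hypothesis of no association is supported only when the data exclude differences large enough to matter. In a small study, failing to find a difference is likely whether or not one exists. Confounding adds to this. Procedure follows tissue and tension, and Aim 1 itself hypothesises that presurgical anatomy predicts procedure, so selection could hide a real difference or create a false one. Neither tissue amount nor tension is among the listed covariates.

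What is at stake is a statement about two operations in wide use. If a non-significant result were set beside a written hypothesis that procedure type is not associated, it could be reported as a hypothesis borne out, and then cited as evidence that anatomy matters and technique does not.

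**Working it through.** **1. The plan's own number.** The target is 30, attrition 30% and enrolment 39.
- 30 x 1.30 = 39 reproduces the stated enrolment.
- The expected number remaining is 39 x 0.70 = 27.3, about 27. Leaving 30 would need 30 / 0.70 = 42.9, so 43.
- The article gives no power calculation to reproduce. The figures below use 27, with 30 as a check.

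**2. Assumptions, since the article gives no values.** Two-sided 5% level; two groups with a common SD; IVV/DOZ split from 13/14 to 20/7; SD of the 0-6 stop count 1.5 to 2.0. Results in SD units apply to a continuous anatomical measure as well as to the stop count, so they hold for either reading of the clause. Levator continuity is yes/no and is not covered.

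**3. Precision.** Half-width = t(0.975, n1 + n2 - 2) x sqrt(1/n1 + 1/n2), in SD.
- 13/14: 2.06 x 0.385 = 0.79 SD
- 20/7: 2.06 x 0.439 = 0.90 SD
- 15/15 (the full 30): 2.05 x 0.365 = 0.75 SD

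In stops, 0.79 SD is 1.2 (SD 1.5) to 1.6 (SD 2.0), and 0.90 SD is 1.4 to 1.8, on a scale of six.

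**4. Chance of a significant difference when one exists** (noncentral t, noncentrality = d / sqrt(1/n1 + 1/n2)).

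| True difference | 13/14 | 20/7 | 15/15 |
|---|---|---|---|
| 0.5 SD | 24% | 19% | 26% |
| 0.8 SD | 52% | 42% | 56% |
| 1.0 SD | 70% | 59% | 75% |

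At 0.5 SD with 27 infants, the result is non-significant about 76% to 80% of the time. Losing 5 degrees of freedom to covariates moves the 27-infant figures by about one percentage point or less.

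**5. Chance of showing equivalence if the true difference is zero** (two one-sided 5% tests, 27 infants).
- Margin 0.5 SD: 0.3% or less (0.6% with 15/15)
- Margin 0.8 SD: 14% to 30%
- Margin 1.0 SD: 43% to 62%

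For 80% power, n per group = 2 x ((1.645 + 1.282) / margin)^2. This gives 69, 27 and 18 per group, or 138, 54 and 36 in all. The expected 27 infants fall short of each.

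**6. The two readings against the planned analysis.**
- *Anatomy does not differ by procedure.* The surgical-type factor in the analysis of covariance addresses this, but as an ordinary factor test. One named feature is a longer velum, while the article describes DOZ as lengthening it.
- *Stop diversity does not differ by procedure.* In the planned model, stops and surgical type are both explanatory factors for anatomy. No term compares stops between procedures, so the clause has no matching analysis.

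**The case against.** The strongest reply is that this is a few words in a study that calls itself a pilot and exploratory, and that admits under Strengths and Limitations a reduced ability to detect subtle effects. Expecting no procedure difference in speech is also consistent with part of the background: similar insufficiency rates, and no technique consistently superior. Estimates with intervals are ordinary content for an analysis plan that is not shown, so their absence from an article is no fault.

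Much of this stands, and it rules out several stronger readings that a reader might infer:

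- *The study is almost certain to confirm the clause whatever the truth.* The figures do not say so: at a true difference of 1.0 SD, power is 59% to 70% with 27 infants.
- *A null result will be taken as no association.* The article states no such rule. It could be misread that way; nothing shows that it will be.
- *The planned analysis tests stop diversity against procedure.* It does not, because anatomy is the outcome.
- *The article's own background predicts a procedure difference in speech.* It is mixed. The cited review on secondary surgery points one way and the statements of similar results point the other. Even the velar-lengthening point is a tension, not a strict contradiction, since selection into procedures could offset lengthening.

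What the reply does not remove is the clause itself. It is a written hypothesis, not an omission, and the general caveat on sample size is never tied to it.

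**Conclusion.** The point holds in limited form. The Aim 2 hypothesis contains a no-association clause whose meaning is unclear and which this design cannot support on either reading. An IVV-DOZ difference would be known only to within about 0.8 to 0.9 SD either way. A moderate true difference of 0.5 SD would be missed roughly three times in four or more, and equivalence within 0.5 SD is practically out of reach. These figures rest on an assumed 5% level and group split; the figures in stops also rest on an assumed SD. Using 30 infants instead of 27 does not change the conclusion. Confounding by the surgeon's choice comes on top and is not captured by the intervals. The consequence is a risk of misreading, not an error in a planned test. It is worth correcting because the change is small and, at the article's status date, data analysis had not begun.

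**What to change.** Delete the words on procedure type from the Aim 2 hypothesis; Expected Findings already restates it without them. In their place, state that the IVV-DOZ differences in stop diversity and in the postsurgical anatomical measures will be reported with 95% CIs as exploratory estimates, confounded by the surgeon's choice of procedure, and that a non-significant result will not be read as no association.

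The cost is one hypothesis given up and a few extra estimates to report. No change to recruitment, data collection or surgical care is involved.
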